### Aims and objectives

The aim of this study is to explore the feasibility and impact of providing early enhanced occupation-based therapy, including cognitive stimulation and activities of daily living, to patients in intensive care. The intervention will focus on cognitive stimulation and engagement in functional activities in mechanically ventilated patients within an intensive care setting. This will be explored through a pilot feasibility trial comparing standard care to daily early enhanced occupation-based therapy. It is hypothesised that critically ill mechanically ventilated patients who participate in the intervention will demonstrate increases in functional ability, cognition and participation compared to those patients who receive standard care. Feasibility aspects of the intervention to be investigated include whether occupational therapy can be provided consistently to a partially sedated population, as well as within a medical setting where environment and medical equipment may limit interventions.

The study is divided into two parts: Part 1 aims to investigate the feasibility of early enhanced occupation-based therapy in a medical/surgical intensive care unit. Part 2 aims to explore the perceptions of participants and their significant others in relation to the therapy experience. Both parts of the study are carried out concurrently.

Specifically, the objectives of the early enhanced occupation-based therapy (the intervention) are:

Part 1:
To evaluate the utility of a selection of functional, cognitive, physical and quality of life outcome measures in their ability to capture the effect of the intervention on participants and their long-term outcomes.To identify recruitment and consent rates from eligible participantsTo evaluate retention rates in response to follow up procedures (attendance at interviews)To test the intervention in terms of therapist compliance, ability to provide consistent intervention (fidelity), differentiation from current usual practice and amount of staff skill/experience required to carry out the interventionTo explore the effect of the intervention on occupational performance at intensive care and hospital discharge, and to evaluate the effect on cognitive, functional and mood factors on discharge from the intensive care unit and hospital, and at 90 days post-randomisation.

Part 2:
To qualitatively investigate the perception of the occupational therapy intervention with the experimental group participants and their significant others, exploring factors such as experience of participation, satisfaction with treatment content and perceived benefit of participation.

## Methods

### Design

The trial, termed EFFORT-ICU, is a phase II feasibility trial incorporating a mixed methods design. The study follows the guidelines for feasibility trials outlined by the SPIRIT 2013 Statement [39]. EFFORT-ICU is a prospective single-centre, single blinded, equally randomised controlled trial (1:1) comparing standard occupational therapy care to an early enhanced occupation-based therapy. A study overview is shown in Fig. 1. The trial is registered as follows: Australia New Zealand Clinical Trials Registry (ANZCTR): ACTRN12618000374268; prospectively registered on 13 March 2018/https://www.anzctr.org.au.

**Fig. 1 Fig1:**
[figure not shown]
Trial flow chart for EFFORT-ICU

### Ethics/governance

Ethical approval for the study from the Metro South Hospital and Health Service Human Research Ethics Committee (EC00167) and The University of Queensland was gained on 27 April 2018 for a 3-year recruitment study cycle. The trial may be independently audited by the ethics committees at any time. Any modifications to the protocol (for example changes to eligibility criteria, outcomes) will be approved by the ethics committees and communicated to all investigators and the trial registry.

### Reporting

The study results will be reported using the “CONSORT 2010 statement: extension to randomised pilot and feasibility trials” [40].

### Progression criteria to decide whether to proceed with RCT

As randomised controlled trials involve a significant organisational and financial input, the decision to progress from a pilot study requires clear and objective measures to ensure that staffing and patients benefit from participation in a study. The use of the guidelines and key information to consider, as proposed by Avery et al. (2017) [41], will influence the evaluation as to whether the trial should progress. The criteria for progression have been identified while considering the usual trial length for a grant funded study (2–3 years), with a projected trial recruitment of 100–150 patients to ensure improvements in clinical significance is achieved [24]. Targets for retention (75%) outcome measure administration (80%) and intervention completion (50%) were identified to minimise impact of missing data while aligning with clinical expectations for this cohort of patients (Table 1).

**Table 1 Tab1:** Progression criteria for RCT

Domain	Proceed with RCT	Proceed with changes to protocol	Do not proceed unless problem resolution
Recruitment	Recruitment of 30 eligible patients within 6 months	Recruitment of eligible patients within 6–12 months	Unable to recruit 30 patients in 12 months
Retention	Minimum of 75% retention to follow-up	Minimum of 50 % retention to follow-up	Less than 50% retention to follow-up
Completion of intervention	At least 50% complete intervention for 40–60 min per day	At least 50% complete intervention for 20–40 min per day	Less than 50% complete intervention for 20 min per day
Outcome measures acceptability	Able to administer 80% of the outcome measures at each time point	Able to administer 80% of the outcome measures at each time point	Able to administer 80% of the outcome measures at each time point
Adverse events	No serious therapy-related adverse events during trial	Less than 5 serious therapy-related adverse events during trial	Five or more serious therapy-related adverse events during trial

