## Trial status

The trial is recruiting participants but is paused due to COVID-19.

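### The outcome-measure row of the progression table gives the same 80% criterion under all three decisions, so the boundary between amending and stopping is missing

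*Protocol article*

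**What the plan says.** The section on progression criteria explains that "the decision to progress from a pilot study requires clear and objective measures". Table 1 then lists five domains (recruitment, retention, completion of the intervention, acceptability of outcome measures, adverse events) against three decisions, the last of which is headed "Do not proceed unless problem resolution".

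In four of the five rows the entry changes from column to column. In the acceptability row it does not: each of the three cells reads "Able to administer 80% of the outcome measures at each time point".

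The paragraph above the table mentions the same figure once, as a target: "Targets for retention (75%) outcome measure administration (80%) and intervention completion (50%) were identified to minimise impact of missing data". It gives no second figure for outcome measures. The Data analysis section plans to look at how easily the measures can be administered and at missing data, but sets no threshold for a decision.

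**The concern.** A three-tier progression rule works only if a result points to one tier. Here the row assigns the same condition to going ahead, amending and stopping. If administration falls short of 80%, the team would have to decide after seeing the data whether the shortfall calls for amendment or for a halt. Fixing criteria in advance is meant to prevent that.

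A shortfall is plausible. Table 4 schedules six of these measures at ICU discharge (MBI, grip strength, FIM, SF-36v2, HADS, MoCA), five at hospital discharge (the same without SF-36v2) and six at 90 days. The participants have been mechanically ventilated, and the article itself expects delirium and poor attention in some of them and lists attrition at follow-up as a risk. The utility of the outcome measures is also the first Part 1 objective. Ease of administration is only part of that objective, but this is the one progression row that tests it.

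**Working it through.** The plan contains no calculated figure to reproduce. The check is whether each possible result leads to exactly one decision.

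**Inputs.** The three cells of the acceptability row and, for comparison, the three cells of the retention row, all from Table 1. Let x be the share achieved. The entry 'able to administer 80%' is read as x ≥ 0.80.

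**Acceptability row, as written**

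| x | Proceed (x ≥ 0.80) | Proceed with changes (x ≥ 0.80) | Do not proceed (x ≥ 0.80) |
|---|---|---|---|
| 0.30, 0.50, 0.60, 0.75, 0.79 | no | no | no |
| 0.80, 0.90, 1.00 | yes | yes | yes |

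No value of x selects exactly one column.

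**Retention row, as written**

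| x | Proceed (x ≥ 0.75) | Proceed with changes (x ≥ 0.50) | Do not proceed (x < 0.50) |
|---|---|---|---|
| 0.30 | no | no | yes |
| 0.50, 0.60 | no | yes | no |
| 0.75 to 1.00 | yes | yes | no |

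The two upper retention cells are nested, so the natural reading is to take the best tier met. On that reading every x gives one decision. The same reading does not rescue the acceptability row. Taking the best tier met gives 'proceed' at 80% or more, but below 80% there is still no entry to apply.

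**What the prose adds.** The single 80% target supports x ≥ 0.80 as the proceed condition. It follows that x < 0.80 means not proceeding unchanged. It does not say where, below 0.80, amending ends and stopping begins.

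**Check of the completion row.** Take 40% of participants at 40–60 min per day, 40% at 20–40 min and 20% below 20 min. If "At least 50% complete intervention for 20–40 min per day" is an exclusive band, it holds 40% and is not met. Proceed is not met (40% < 50%), and stop is not met because 40% + 40% = 80% reach 20 min. If the cell is read cumulatively, as the retention row must be, 80% ≥ 50% and the result is 'proceed with changes'. One decision follows.

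**The case against.** The strongest reply is that the row is less empty than it looks. The prose target makes 80% recoverable as the proceed threshold, and the repeated sentence may come from one merged cell spanning three columns in the typeset table. Both points are fair. The first means that the row does carry information, and a claim that it can return no decision at all would go too far. The second would remove the oddity of 80% counting as a reason to stop, but would leave one criterion and no tiers. The lower boundary is missing either way.

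It can also be said that Table 1 informs a judgement and is not a mechanical rule, that the stop column allows for resolution of the problem, and that the full protocol is held in the registry. These points limit the importance. They do not correct a row that the article prints with three identical entries.

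A reader might infer more, namely that two other rows also fail. The documents do not support that.

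- **Completion.** The apparent gap exists only if the middle cell is read as an exclusive band. A cumulative reading closes it.
- **Recruitment.** The stop cell is "Unable to recruit 30 patients in 12 months", and the Trial status section says "The trial is recruiting participants but is paused due to COVID-19". Nothing says that paused months count towards the limit, and no recruitment start date is given. The interval of about 34 months from ethics approval (27 April 2018) to publication (18 February 2021) is therefore not a recruitment time. The middle recruitment cell omits the number 30, but the cells on either side make it clear.

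**Conclusion.** The point holds for the acceptability row. As printed, the row cannot separate the three decisions: at 80% or more all are met, and below 80% none is. With the prose target, the proceed threshold can be taken as 80%, but the amend/stop boundary cannot be found in the document. This rests on reading the table text as given and on 'able to administer 80%' meaning at least 80%.

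The extent is one of five progression domains. Randomisation, participant safety and the between-group comparisons do not depend on it. It still deserves correction, because the progression decision is a main product of a feasibility trial and this row is silent in the range where a rule would be needed. The documents do not show that the completion or recruitment rows would misclassify the trial. Those are matters of wording only.

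**What to change.** Replace the acceptability row with three bands applied to one quantity: the lowest administration rate across ICU discharge, hospital discharge and 90 days, among participants alive and still in the trial at each time point.

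- **Proceed:** lowest rate at least 80%.
- **Proceed with changes:** lowest rate below 80% but at or above a stated floor.
- **Do not proceed unless resolved:** lowest rate below that floor.

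Using the lowest rate keeps the bands exclusive when time points differ. Rates of 85%, 60% and 40%, for example, are judged on 40% alone. Stating the limits as inequalities leaves no gap, so 79.5% falls below the proceed threshold.

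The documents give no figure for the floor. The sponsor should choose and justify one. The 50% in the retention row is one option, but it is an assumption, since retention is a different quantity. The trial has already been recruiting, and the data forms are reviewed weekly for missing data, so administration rates may be partly known. The amendment should disclose that the floor was set after recruitment began.

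Three minor clarifications can be made at the same time:

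- Word the middle completion cell as at least 50% completing 20 min or more per day, with the proceed criterion not met.
- Add 30 to the middle recruitment cell.
- State whether months paused for COVID-19 count towards the recruitment limits.

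The cost is table wording, ethics committee approval and a registry update, which the Ethics/governance section already foresees for protocol changes. No new data are needed.

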### Participants

The study will be conducted in a Queensland level two adult eight-bed intensive care unit at Logan Hospital, Brisbane, Australia. All patients admitted to the intensive care unit will be included if they are aged over 18 years and are expected to require invasive mechanical ventilation for greater than 48 h.

Patients will be excluded from the trial if:
They are admitted to the intensive care unit but do not require mechanical ventilation.They have been readmitted to the intensive care unit from the current hospitalisation.A withdrawal of treatment is expected to occur within the next 24 h or they are not expected to survive the current intensive care unit admission.They have a poor level of functional ability prior to admission (requiring carer assistance/high dependency level in activities of daily living as measured by a Modified Barthel Index score < 40).They have a pre-existing severe cognitive deficit (as identified by completion of the short form IQCODE with an average score above 3.31–3.38).They have a pre-existing significant mental health disorder impacting on participation.They live interstate and would be unable to attend the 90 days post-randomisation follow-up in person.They are unable to communicate in English.

Patients admitted over the weekend where occupational therapy intervention cannot be immediately initiated will be eligible to participate in the trial, and therapy will begin on the first working day.

The 90-day post-randomisation evaluations’ timepoint for the follow-up review date has been chosen based on the funding cycle. As this is a pilot feasibility study and the study is limited in duration, this time point was chosen to be sufficiently representative to identify if patients had ongoing concerns, and to ensure their memory of the therapy provision was current for the semi-structured interviews.

### Recruitment

A consecutive sampling model will be used where all patients who meet the eligibility criteria will be invited to participate. All patients admitted to the intensive care unit will be screened for eligibility on a daily basis by clinical staff. Patients meeting the study criteria will be referred to the research team within 24 h of admission. Written informed consent will be sought. Eligible participants will begin treatment after 48 h and before 72 h have elapsed since admission. The trial staffing has been adjusted to guarantee occupational therapy cover can be provided consistently Monday to Friday irrelevant of public holidays. This ensures that all patients have fair access to daily therapy within a working week irrespective of the time of year recruited.

### Consent

Participants will be invited to provide consent at the time of recruitment if able to do so. If due to medical conditions, the participant is unable to provide informed consent, the person responsible will be approached to provide consent on their behalf. In addition, informed consent will be sought from the person responsible to act as a significant other participant during the qualitative interviews in part 2. Once a participant is able to provide their own consent, they will be given an opportunity to continue with the trial or withdraw. Eligible participants will be informed that participation in the study is voluntary and if they choose not to participate, or if they choose to withdraw from the study after consenting, this will in no way affect their normal treatment at the hospital.

The study will be explained verbally by the chief investigator or nominated delegate. The participant or person responsible will be given the opportunity to read the information sheet and ask any questions prior to participation in the study. The participant or person responsible will be provided with a copy of the signed consent form and the information sheet and any other documentation discussed throughout the consent process.

### Randomisation and blinding

Following consent, participants will be randomly allocated to either the intervention group who will receive early occupation-based activity or the control group who will receive standard occupational therapy, medical, nursing and physiotherapy care. Patients will be randomised into the intervention and control groups via computer-generated numbers (http://www.randomization.com/) which will be sealed in consecutively numbered opaque envelopes. The production of the envelopes will be performed by research support staff who will not be involved in the interventions.

### Blinding

It will not be possible to blind the research team or the participants to group assignment. However, participant outcome measurement assessors will be blinded to participant assignment. The blind assessors will be other occupational therapists who work at the hospital but not in the intensive care unit, or with patients who have been transferred from intensive care.

### Interventions

#### Control group

The control group will receive usual occupational therapy care. At Logan Hospital, an occupational therapist attends daily clinical ward rounds within the intensive care unit. Patients are identified based on clinical needs and daily prioritisation guidelines for operation within an acute hospital. Core non-functional risk remediation activities such as splinting (for example to prevent foot drop) and pressure cushion provision are provided on an immediate basis when clinical need is identified. Functional therapy is completed at the discretion of therapists and clinical caseload weighting and may be absent in most units. The usual care group in this trial will therefore not receive any therapy unless an urgent splinting need is required to maintain range of movement. Administration of the daily outcome measures which includes the Multiple Status Questionnaire (MSQ) by the blinded bedside nurse is not anticipated to take longer than 10 min per day. Any intervention provided to the control group will be documented and included within the analysis.

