**Methods:**

This study involves a single site randomised-controlled feasibility trial comparing standard occupational therapy care to an early enhanced occupation-based therapy. Thirty mechanically ventilated ICU patients will be recruited and randomly allocated to the intervention or control group. The primary outcome measure is the Functional Independence Measure (FIM), and secondary measures include the Modified Barthel Index (MBI), Montreal Cognitive Assessment (MoCA), grip strength, Hospital Anxiety and Depression Scale (HADS) and Short-Form 36 Health survey (SF-36). Measures will be collected by a blind assessor at discharge from intensive care, hospital discharge and a 90-day follow-up. Daily outcome measures including the Glasgow Coma Scale (GCS), Richmond Agitation and Sedation Scale (RASS) and Confusion Assessment Measure for intensive care units (CAM-ICU) will be taken prior to treatment. Participants in the intervention group will receive daily a maximum of up to 60-min sessions with an occupational therapist involving cognitive and functional activities such as self-care and grooming. At the follow-up, intervention group participants will be interviewed to gain user perspectives of the intervention. Feasibility data including recruitment and retention rates will be summarised descriptively. Parametric tests will compare outcomes between groups. Interview data will be thematically analysed.

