#### Intervention group

Early enhanced occupation-based therapy is limited in the ICU. Identification of appropriate occupation-based therapy is dependent on cognitive (arousal, attention, executive functioning), physical (strength, co-ordination) and physiological restrictions (ventilator, cardiovascular status, medications). Co-morbidities, such as delirium, are assessed daily prior to the session and may result in session adaptation to maximise participation. Prior to engaging in early enhanced occupation-based therapy with the therapists, all patients will have received daily medical clearance by the treating physician. Clear physiological norms are established prior to participation to ensure that the occupation-based therapy is within the physiological capabilities of the participant [42]. A precautions checklist will be completed prior to each therapy session to ensure medical stability and clearance for activity participation. The checklist was created based on expert consensus guidelines for mobilisation in the intensive care unit and adapted to functional and cognitive participation requirements [42]. See Table 2 for contraindications to treatment. Monitoring of cardiovascular and respiratory status during early enhanced occupation-based therapy is completed by the bedside ICU nurse. Session termination will be under the guidance of the bedside nurse in collaboration with the occupational therapist and will be based on changes in cardiac and respiratory function as well as patient request to stop. Any immediate change that results in a contraindication being identified will lead to session termination. Further guidance on therapy discontinuation will be in line with published guidelines for exercise termination [43, 44] and includes a drop in systolic blood pressure, signs of myocardial infarction, unusual shortness of breath, arrhythmias, angina or signs of poor perfusion.

**Table 2 Tab2:** Checklist for contraindications to intervention

- O_2_ Saturation < 90% - Respiratory Rate > 30 bpm - Fi O_2_ > 0.6 - PEEP > 10 cm H_2_O/ventilator dysynchrony - Any rescue therapies (NO, Prostatcyclin, prone) - Significant antihypertensive medications - MAP (below target, various support measures) - Bradycardia on significant pharmacological support - Tachycardia > 150 bpm - RASS > 2+ - Large open wound/uncontrolled active bleeding	

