Patients will undergo sedation breaks during which targeted early enhanced occupation-based therapy will be delivered. The therapist will carry out the intervention to a maximum of 60 min per day, based on graded performance and localised adaptation from response level, such that sessions may be carried out twice a day (30 min each) to 3 times a day (20 min each) or a single session with a higher level patient (60 min). The measure of 60 min has been chosen to comply with perceived expectations of rehabilitation unit therapy intensity and duration per profession [45]. Where the full quota of therapy is unable to be provided, clear reasons for therapy termination will be gathered on the data form and analysed.

Prior to engaging the patient in early enhanced occupation-based therapy, participants will undergo simple cognitive and physical assessments to enable the therapist to adapt the chosen task to optimise performance and ensure that cognitive stimulation is appropriate. Pre-intervention measures include the following:

Richmond Agitation and Sedation Scale (RASS) [46] measures level of sedation and agitation. Patients will receive treatment if they fall within − 2 to + 2 scales. Patients falling on either extremes are deemed unsuitable for engagement at the current time point, although will be assessed regularly throughout the day prior to therapy, to ensure all opportunities for engagement are taken.

Glasgow Coma Scale (GCS) [47] measures arousal and response level in patients with severe injuries and is used to identify initial emergence of recovery post-sedation withdrawal. The highest score is 15 (fully oriented and alert) and the lowest score is 3 whereby a patient is considered unresponsive. The GCS will be completed prior to the treatment intervention as this will guide the therapist in providing either sensory stimulation [48, 49] or early enhanced occupation-based therapy.

The Confusion Assessment Measure ICU (CAM-ICU) [50] is an assessment of confusion in the early identification of delirium of patients within the intensive care unit. The presence of delirium will not limit participation within an early enhanced occupation-based therapy session. Strategies will be used to increase attention and encourage sequencing of short subtasks in order to complete a full grooming or self-care task.

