#### Secondary outcome measures

The Modified Barthel Index (MBI) [63] is used to measure functional ability and serves as a secondary measure included for its ability to detect change within self-care and functional tasks. The MBI is commonly used in hospital settings, although recent research has highlighted ceiling effects and lack of reliability [64]. The MBI also provides an additional source of comparison across multiple earlier critical care rehabilitation studies. The MBI will be used at multiple time points including allocation to intervention, intensive care unit discharge, hospital discharge and 90-day post-randomisation follow-up.The Montreal Cognitive Assessment (MoCA) [65] is a screening measure of cognition and assesses multiple domains of cognition including attention, memory and visuospatial relations. It is commonly used within the acute and community setting and demonstrates high criterion and convergent validity within the acute care setting [66]. The MoCA will be administered at discharge from intensive care unit, hospital and 90-day post-randomisation follow-up using alternate versions at each time point [67].Grip strength will be measured using a dynamometer (Jamar) [68] at discharge from intensive care unit and hospital and 90-day post-randomisation follow-up. Grip strength is used as a measure of intensive care unit-acquired weakness (ICUAW) and infers a relation between weakness and inability to complete functional activities independently [69].The Short-Form (36) Health Survey (SF-36v2™) will provide a baseline and post discharge measure of participants’ health-related quality of life (HRQOL). The SF-36v2™ is a validated and reliable tool [70] and has been further validated within the critical care setting [71]. This will be completed at intensive care unit discharge and 90-day post-randomisation follow-up.Sedation and delirium status will be measured using the validated Richmond Agitation Sedation Scale (RASS) [46] and the reliable and validated Confusion Assessment Method for ICU (CAM-ICU) [50]. These scores are regularly administered by nursing staff throughout a 24-h period. RASS and CAM-ICU scores immediately prior to and following early occupation-based interventions will be collected for additional analysis. RASS and CAM-ICU scores for the control group participants will be collected daily at 9am.The Glasgow Coma Scale (GCS) [72] is used to evaluate the level of consciousness in patients with neurological conditions or severe injury [73] and will be collected daily at 9 am in the control group, and pre-treatment in the intervention group.Hospital Anxiety and Depression Scale (HADS) [74] is a measure of emotional distress regarding anxiety and depression. It has been validated with the use of critical care survivors [75]. It will be administered at discharge from intensive care unit, hospital and 90-day post-randomisation follow-up.The Informant Questionnaire on Cognitive Decline in the Elderly (IQCODE) (short form) [76] is a reliable and validated measure used to screen for cognitive dysfunction. It will be used as a screening tool for eligibility to the trial and will be completed by the participant’s person responsible.The Short Portable Mental Status Questionnaire (MSQ) [51] is a brief orientation checklist used to demonstrate current and previous memory linked to orientation. It is a 10-statement questionnaire that is easily administered at the bedside. It will be completed pre-and post-treatment in the intervention group, and at 9 am in the control group.

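### The bedside nurse who takes the daily measures is called blinded but attends and helps to end the therapy sessions, so the daily secondary measures are not blinded

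*Protocol article*

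**What the plan says.** Under Control group, in a sentence about how long the assessments take, the protocol article refers to "Administration of the daily outcome measures which includes the Multiple Status Questionnaire (MSQ) by the blinded bedside nurse".

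Under Intervention group it says: "Monitoring of cardiovascular and respiratory status during early enhanced occupation-based therapy is completed by the bedside ICU nurse". On ending a session it says: "Session termination will be under the guidance of the bedside nurse in collaboration with the occupational therapist".

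The Blinding section states that "participant outcome measurement assessors will be blinded to participant assignment" and identifies them: "The blind assessors will be other occupational therapists who work at the hospital but not in the intensive care unit". The abstract ties blind assessment to three time points: "Measures will be collected by a blind assessor at discharge from intensive care, hospital discharge and a 90-day follow-up". It mentions the daily measures in a separate sentence that makes no blinding claim.

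RASS, CAM-ICU, GCS and MSQ all appear under Secondary outcome measures and as daily entries in Table 4. On RASS and CAM-ICU that section says: "These scores are regularly administered by nursing staff throughout a 24-h period". In the intervention arm, RASS, CAM-ICU and MSQ are recorded before and after therapy and GCS before it. In the control arm all four are recorded at 9 am. Data management says that the investigators and therapists who deliver the intervention collect all participant data.

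**The concern.** CAM-ICU, RASS and MSQ need judgement from the rater at the bedside. A rater who knows the allocation, and expects stimulated patients to be clearer, may score them as clearer. Blinding is meant to rule this out, and the article claims it for the person who administers the daily measures while giving the bedside nurse a working part in the intervention.

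What is at stake is how any difference between arms in delirium, sedation or orientation during the ICU stay is read. If the Control group wording is carried into the report, such a difference would appear to come from a masked assessment. The trial is meant to inform a phase III design, so the misdescription could be carried forward.

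**Working it through.** The article states no figure on this point, so the check is a comparison of its sections.

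1. **Who takes the daily measures.** Control group: the bedside nurse, described as blinded. Secondary outcome measures: nursing staff for RASS and CAM-ICU, with no distinction between arms.

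2. **What the bedside nurse does in the intervention arm.** Intervention group: observes the patient during therapy and guides its termination together with the occupational therapist. That nurse sees the intervention delivered and so knows the allocation.

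3. **What the bedside nurse sees in the control arm.** Control patients receive no therapy except for an urgent splinting need. Intervention patients may have one, two or three sessions a day, up to 60 min in total, in an eight-bed unit. A nurse whose patient has no sessions over several days can often infer control. The inference is not certain, because an intervention patient can also miss sessions.

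4. **Whether timing conceals the arm.** It does not. Scores taken around a session in one arm and at 9 am in the other themselves indicate allocation.

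5. **Whether masking is described elsewhere.** No section names a separate nurse rater or a procedure to keep the bedside nurse unaware. The Blinding section's definition of the assessors leaves bedside nurses out. The Limitations section acknowledges lack of blinding only for the therapists who deliver therapy.

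6. **Who rates MSQ and GCS in the intervention arm.** Before therapy, "participants will undergo simple cognitive and physical assessments to enable the therapist to adapt the chosen task". This gives the purpose of the scores, not the person who takes them. Data management points to the treating therapists, but collecting data may mean only completing the case report forms. The two candidates are the treating therapist and the bedside nurse, and neither is blind.

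7. **What lies outside the point.** The Primary outcome measure section assigns the FIM to a blinded occupational therapist who does not work in the ICU. That does not depend on the bedside nurse.

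Steps 1 and 2 contradict each other, and steps 3 to 5 offer nothing that resolves the conflict.

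**The case against.** The strongest reply is that this is one misplaced adjective. It occurs once, in the control section, in a sentence about time burden. The article never says that the intervention-arm raters of the daily measures are blinded, and the abstract and the Blinding section already reserve blind assessment for occupational therapists at the later time points. No progression criterion in Table 1 uses a comparison of daily scores between arms. The next trial is to be sized on the primary outcome, and the article says that the present one is not powered.

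Most of this stands, and it limits the weight of the point. It does not remove the contradiction. The word is a positive statement about the rater of listed secondary outcomes, and the Data analysis section does not exclude those outcomes from its between-group tests.

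Three stronger readings are tempting, and the document does not support them:

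- **That different professions rate the two arms.** For RASS and CAM-ICU the text points the other way, to nursing staff throughout. For MSQ and GCS it is possible but not established.
- **That the nurse knows control allocation as surely as intervention allocation.** Intervention patients can go without sessions because of the Table 2 contraindications, a RASS score outside the treatable range, or a weekend.
- **That the bias amounts to a given number of percentage points.** Any such figure would need an assumed rate of misclassification. The article gives none and defines no delirium-day endpoint to which it would apply.

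**Conclusion.** The blinding claimed for the daily measures does not hold as written. It concerns four secondary measures (RASS, CAM-ICU, GCS and MSQ) in a feasibility trial of 30 participants. The consequence is for interpretation: differences between arms in these scores must be treated as unblinded. The direction and size of any bias cannot be derived from the document.

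The conclusion assumes that the bedside nurse in the two sections is the same role, which is how the article uses the term, and that no masking arrangement exists beyond what it describes. A reader might go on to infer that assessor blinding fails for the trial as a whole. This contradiction does not show that, because the FIM and the other discharge and 90-day measures rest on separate assessors. Data management sits uneasily with that arrangement and needs to be reconciled, but it does not by itself show that those assessors are unblinded.

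**What to change.** 1. In the Control group section, delete the word blinded for the bedside nurse. State that RASS, CAM-ICU, GCS and MSQ are unblinded.
2. Limit the assessor-blinded claim explicitly to the measures taken at ICU discharge, hospital discharge and 90 days.
3. Base any comparison of RASS and CAM-ICU between arms on the routine scores that nursing staff already take in both arms. This makes the rater's role the same in each arm, although it does not make the scores blind.
4. Report MSQ and GCS descriptively and as unblinded, unless the sponsor names one role to rate them in both arms. No routine nursing score of either is described for the intervention arm, so a same-role comparison would need a new procedure.
5. Reconcile Data management with the Blinding and Control group sections by saying who rates each measure and who only records it.

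Items 1, 2 and 5 are wording. Item 3 uses scores already being taken. The cost is a less favourable blinding statement for these secondary measures, plus a modest change of procedure if MSQ and GCS are to be compared between arms.
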